## Abstract

**Background:**

Bacterial resistance development is one of the most urgent problems in healthcare worldwide. In Europe, dentistry accounts for a comparatively high amount of antibiotic prescriptions. In light of increasing levels of bacterial resistance, this development is alarming. So far, very few interventional studies have been performed, and further research is urgently needed. By means of a complex educational intervention, the DREAM trial aims at optimising antibiotic prescribing behaviour of general dentists in Germany.

**Method:**

This is a cluster-randomised controlled trial, where each cluster consists of one dental practice and all of its patients in a defined period. Participants are general dentists practicing in the German region of Mecklenburg-Western Pomerania. Randomisation takes place after baseline data collection (6 months) and will be stratified by the antibiotic prescribing rates of the participating dental practices. Dentists randomised into the intervention group will participate in a complex small group educational seminar that aims at: increasing knowledge on bacterial resistance, pharmacology, and prophylaxis of infectious endocarditis; increasing awareness of dentist-patient communication using video-taped vignettes of dentist-patient communication on antibiotic treatment; improving collaboration between general dentists, general practitioners, and practice-based cardiologists on the necessity of antibiotic prophylaxis; enhancing awareness of the dentists’ own prescribing habits by providing antibiotic prescribing feedback; and increasing patient knowledge on antibiotic treatment by providing patient-centred information material on antibiotic prophylaxis of endocarditis. The dentists randomised into the control group will not receive any educational programme and provide care as usual. Primary outcome is the overall antibiotic prescribing rate measured at T1 (period of six months after intervention). In a subgroup of adult patients affected by odontogenic infections, microbiological analyses for antibiotic resistance of oral streptococci are performed.

**Discussion:**

Major aim of the study is to improve the process of decision making with regard to antibiotic prescribing. The approach is simple to implement and might be used rapidly in graduate and post-graduate medical education. We expect the results of this trial to have a major impact on antibiotic prescription strategies and practices in Germany.

**Trial registration:**

Current Controlled Trials ISRCTN09576376

## Background

Rising levels of bacterial resistance are one of the most urgent problems in healthcare worldwide. The overuse and the misuse of antibiotics are the basic reasons for this development. Studies consistently confirm the association between antimicrobial consumption and bacterial resistance [1]. As a consequence, in order to reduce and slow down the global threat of bacterial resistance development, it is very important to reduce the inappropriate use of antibiotics. Antimicrobial drugs should be reserved to patients who actually benefit from the treatment.

Apart from this severe global development, at the individual level, treatment with antibiotics correlates with drug-related adverse reactions, such as diarrhea or allergic reactions. Especially, if antibiotics are not indicated, these reactions outweigh any benefit of the treatment [2].

Prescribing non-indicated antibiotics also has an impact on healthcare expenditures. Both unnecessary consumption of antibiotics and treatment of preventable drug-related adverse reactions, including hospital stays, put a huge financial burden on national healthcare systems. Optimising the use of antibiotics will decrease this burden [3].

Data on outpatient antibiotic use show that since 1997 daily defined doses per 1,000 inhabitants per day (DID) have increased in Europe. At the same time, prescriptions of broad spectrum antibiotics have become more common, while narrow spectrum antibiotics have been used less [4,5]. This development is fostering further bacterial resistance. With 7% of all antibiotics used in primary care, dentistry accounts for a comparatively high amount of antibiotic prescriptions [6]. Studies indicate a non-conforming use of antibiotics as well as a suboptimal choice of antimicrobial substances as far as guideline recommendations are concerned [7,8]. In light of increasing levels of resistance, this development is alarming [6].

As to general dentistry in Germany, little data exists. However, comparing absolute numbers of antibiotic prescriptions in primary care, dentists are fourth, following general practitioners, internal specialists, and pediatricians [9]. Data of German statutory health insurances on the year 2010 show that, on average, dentists prescribed two antibiotics per week. Interestingly, in derogation from national and international guidelines, German general dentists seem to favor clindamycin over preferably recommended substances [10]. A study performed in northern Germany and based on postal questionnaires shows similar results [11].

Optimising antibiotic prescribing in general dentistry might contribute to decreasing levels of antibiotic resistance development and thereby increase the quality of healthcare provision in general. In the past, several interventional randomised controlled trials (RCTs) from other medical fields were successful in optimising antibiotic prescribing. Most of these studies focused on respiratory tract infections, the disease that causes most antibiotic misuse and overuse in primary care. Results show that complex interventions that aim at changing behaviour rather than just providing information are most efficient [1,12-14].

Concerning dentistry, very few interventional studies have been performed so far. Palmer *et al.*, for example, collected data of antibiotic prescribing among general dentists six weeks before and after an audit that included educational components and the provision of guidelines. Antibiotic prescriptions decreased by 42.5%. Above that, guideline conformity could be improved [15]. Despite the very promising results, the study lacked a long-term follow-up. In a three-armed RCT performed by Seager *et al.*, the efficiency of educational outreach visits was compared to the provision of information material by mail in an intervention group and to no intervention in a control group. The educational outreach visits were successful in reducing prescribing rates significantly and also improved prescribing appropriateness [16]. In the field of dentistry, where a high potential for reducing non-indicated antibiotics exists, further research is urgently needed.

To investigate the underlying reasons for inadequate antibiotic treatment in German general dentistry, within the DREAM trial we performed extensive qualitative research. Narrative in-depth interviews with dentists revealed areas and situations of non-indicated antibiotic prescribing. These include treatment of patients during emergency services or shortly before weekends or holidays when, due to a lack of time and/or follow-up, dentists were inclined to prescribe antibiotics. Moreover, the treatment of patients suffering from multimorbidity was perceived as a challenge. Both the lack of medical knowledge on cardiac impairments and the fear of judicial consequences induced dentists to prescribe antibiotics for safety reasons. Based on these results, approaches to solve these challenging situations were developed. Especially with regard to their acceptability and practicability, these approaches were discussed extensively among dentists by means of focus group discussions. The results contributed significantly to the development of the complex intervention.

### Objectives

By means of a complex educational intervention, the cluster-randomised controlled DREAM trial aims at optimising antibiotic-prescribing behaviour of general dentists in Germany. The complex educational intervention is based on narrative in-depth interviews and focus group discussions with dentists and includes transfer of relevant knowledge, dentist-patient communication, improved collaboration with physicians from other fields, antibiotic prescribing feedback, and patient education. The trial will test the efficiency of the intervention. In addition, the study contains a subset of microbiological analyses on antibiotic resistance among a subgroup of patients affected by odontogenic infections.

## Methods

### Trial design

A cluster-randomised controlled trial (cRCT) will be performed. Clusters are employed to avoid contamination between the intervention and the control group. Each cluster will consist of one general dentist practice and all of its patients during a defined period. Prior to randomisation, baseline data will be collected over a period of six months (T0) to adjust for inter-cluster imbalances of antibiotic prescribing. After randomisation, the intervention takes place which is followed by two more six-month periods of collecting antibiotic prescribing data (T1 and T2).

### Participants

General dentists with their practices in the German region of Mecklenburg-Western Pomerania are eligible for participation in the trial. Given their highly selective group of patients, dentists with sub-specializations will not be included. Among the participating dentists, antibiotic prescribing data of all patients will be collected.

### Recruitment

All general dentists with a practice in and around 150 kilometers of Rostock (n = 665), the largest city of Mecklenburg-Western Pomerania, will receive postal invitations to take part in the study. These invitations will be sent out in waves and will be based on a random sample of eligible dentists. Participating dentists will receive case payments to compensate for time and effort. The payments are identical in the intervention and the control group. Trained study assistants take care of the enrolment process. Participating dentists provide informed consent before baseline data collection and randomization.

### Randomisation

Cluster-randomisation takes place after baseline data collection. Concealment of allocation is preserved. Randomisation will be stratified by the antibiotic prescribing rates of the participating dental practices and will be performed by a statistician; this will avoid imbalances between the intervention and the control group.

### Blinding

Within the DREAM trial, it will not be possible to blind dentists, study personnel, and statisticians.

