### Outcomes

Primary outcome is the overall antibiotic prescribing rate of the intervention group and the control group measured at T1, thus measured in the interval between months one to six after intervention. A number of secondary outcomes will be analyzed for the subgroup of patients suffering from odontogenic infections (see below).

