### Data collection, completeness, and quality

Data collection will be based on practice software. In Germany, dentists make use of a large variety of software packages. Trained study assistants will visit the participating practices regularly to collect data and to verify data quality by comparing antibiotic prescriptions and number of patient visits with software entries. After data collection, a second study assistant will check the data file for completeness and correctness.

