### Statistical methods

A ‘full analysis set’ (FAS) following the principle of intent-to-treat (ITT) will include every patient as randomised. First, confirmatory analyses on efficacy variables will be performed on the FAS patients. Because imbalances are more likely among cluster-randomised trials than among trials randomised at the patient level, variables related to dentists’ characteristics will already be included in the primary data analysis. Initially, baseline characteristics will be compared between groups. If significant differences are found for variables that could potentially bias the results, data analysis will be based on a comparison of the baseline-adjusted rates of antibiotic prescribing between the intervention and the control group at T1 (primary outcome) and T2. The direct maximum likelihood approach is used as estimation procedure and will provide unbiased estimated values. Analyses for secondary endpoints will be performed in a strictly exploratory way using analogue models.

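### The Blinding section says statisticians cannot be blinded, but the T1 file can be checked and its analysis programmed without arm identity: an avoidable, minor risk of analyst bias

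*Protocol article*

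**What the plan says.** The Blinding section consists of one statement: "it will not be possible to blind dentists, study personnel, and statisticians". It treats the three groups alike and names neither a reason nor a safeguard.

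Four other sections bear on it:

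- **Randomisation:** allocation "will be performed by a statistician". The text does not say whether that person also analyses the data.
- **Outcomes and Data collection:** "Primary outcome is the overall antibiotic prescribing rate of the intervention group and the control group measured at T1", and "Data collection will be based on practice software". Study assistants verify the entries at the practices, and then: "After data collection, a second study assistant will check the data file for completeness and correctness".
- **Statistical methods:** "variables related to dentists’ characteristics will already be included in the primary data analysis", without naming them. Then "Initially, baseline characteristics will be compared between groups", and "If significant differences are found for variables that could potentially bias the results, data analysis will be based on" baseline-adjusted rates.
- **Trial status:** at the end of 2013, practices had been randomised and intervention dentists trained. T1 collection had begun and was due to finish in spring 2014.

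**The concern.** Openness to the people who deliver and receive the seminar cannot be avoided. Openness to the people who clean the file and specify the model can be, and the article presents the two as the same.

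In an open trial, data handling and analysis are the stages where concealment is still available. Here some decisions at those stages call for judgement: whether a baseline variable could bias the comparison, which dentist characteristics are included, and how queries on the file are resolved. Someone who knows which practices were trained can, without intending it, let that knowledge affect such decisions. What is at stake is the credibility of the confirmatory T1 comparison. No sample size, power or significance level is affected.

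**Working it through.** **Step 1. Who needs to know the arm?**

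| Role | Needs or learns the arm? |
|---|---|
| Dentists in the four-hour seminar | Yes, unavoidable |
| Seminar staff | Yes, unavoidable |
| Assistants visiting practices | May learn it on site |
| Second assistant checking the file | Not needed for the task |
| Statistician who randomises | Knows the allocation |
| Whoever programs the T1 analysis | Not needed until the program is run |

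**Step 2. What must the T1 file contain?** Practice identifier, period, number of antibiotic prescriptions, number of patients, dentist characteristics and the T0 rate. Arm is one two-level variable at practice level and can be merged last. Nothing in Data collection or Outcomes prevents this.

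**Step 3. Where does judgement enter?** The adjustment rule is triggered by baseline comparisons only. T0 was complete before T1 data existed, so the branch can be settled, with coded arms, without any T1 outcome. The dentist characteristics can be fixed at the same time.

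**Step 4. Was there still time?** Yes. According to Trial status, T1 collection had only started.

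**Step 5. Can a size be attached?** The article gives no figure to reproduce on this point. An illustrative null simulation was used, with these inputs:

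- 46 practices (Sample size section), taken as 23 per arm.
- 40,000 runs, with simple allocation. The trial stratifies by prescribing rate, which the illustration ignores.
- T0–T1 correlation ρ between practices of 0.3 to 0.8. This is an assumption; the article gives none.
- Unadjusted test: t = Δy / √(s²·2/23), 44 df.
- Adjusted test: t = (Δy − βΔb) / √(s²(2/23 + Δb²/Sxx)), 43 df, where b is the T0 rate.

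| ρ | Fixed adjusted model, two-sided | Stated pre-test rule followed mechanically, two-sided | Either model significant, two-sided | Half of previous column | Arms known, model favouring intervention chosen |
|---|---|---|---|---|---|
| 0.3 | 0.050 | 0.048 | 0.0641 | 0.0321 | 0.0317 |
| 0.5 | 0.050 | 0.043 | 0.0726 | 0.0363 | 0.0369 |
| 0.7 | 0.050 | 0.037 | 0.0824 | 0.0412 | 0.0411 |
| 0.8 | 0.051 | 0.032 | 0.0879 | 0.0439 | 0.0436 |

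A fixed adjusted model favours the intervention falsely in about 0.025 of runs.

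The last two columns decide the matter. An analyst with arms coded A/B who reports the smaller p-value is significant whenever either model is. Under the null, half of those results favour the intervention. That half agrees with the error of an analyst who knows the arms: the largest gap is 0.0369 − 0.0363 = 0.0006, below the simulation standard error of about √(0.04 × 0.96 / 40,000) = 0.001. The inflation therefore comes from freedom to choose the model. Codes alone do not remove it; fixing the model before T1 data are linked to arm does.

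**The case against.** The case against has four parts.

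1. **The statement may be an honest disclosure.** If the randomising statistician also analyses, recoding a file of 46 practices would not blind that person. This stands as a practical limit, and the fix allows for it. It does not make blinding impossible for every statistician, and the article does not offer it as the reason.

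2. **The real protection is pre-specification, and the covariate list may be in an analysis plan that is not shown.** This largely stands. A reader might infer that the covariates will be chosen after looking at the T1 data. The article does not say that: it commits to including dentist characteristics, and leaving their names to an analysis plan is common practice. An unseen plan could supply safeguards, but it would not make the statement in the Blinding section correct.

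3. **The adjustment rule looks only at baseline and, followed mechanically, does not inflate the error** (0.032 to 0.048 above). This stands. Harm would require discretion beyond the stated rule, and nothing in the article shows that it was used.

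4. **The second assistant checks objective records, which leaves little room for arm-dependent judgement.** This also stands, so that step is a weak part of the case. It can nevertheless be done without the arm at almost no cost.

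**Conclusion.** The point holds in a limited form. The Blinding section claims too much: the arm can be withheld from T1 file checking and model programming, even though dentists and seminar staff must know it. Some judgement remains in the primary model, so open arms leave a risk of analyst bias that could be avoided. No bias is demonstrated.

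A reader might infer that unblinded statisticians roughly double the type I error. Taking the smallest p-value over 16 covariate subsets in simulated null trials of 46 practices can give about 9.5%, against 4.8% for a fixed T0-adjusted model. That figure should not be used here. No such search is described in the article, and picking the smallest two-sided p-value does not require knowing which arm is which, so A/B codes alone would not prevent it.

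The conclusion rests on the text of the article and on the ordinary structure of a count file, and on no assumed correlation. Priority: a minor, cheap improvement.

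**What to change.** Revise the Blinding section to say:

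- Dentists and seminar staff are unblinded.
- The arm variable is kept out of the T1 file used for checking and programming, or is coded and used only for the T0 baseline comparison. It is released once data cleaning and the primary model program are locked, including the dentist characteristics and the adjustment decision.
- The allocation key is held apart from the analysis file.
- If the statistician who randomised also analyses and so knows the allocation, the protocol says so, and the primary program is locked before T1 data are linked to arm.

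The cost is one revised statement and a small amount of data handling. No extra staff are needed if the key is kept separate, and no sample size, power or significance level changes.

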### Intervention

After randomisation, dentists of the intervention group will participate in a four-hour, small-group intervention seminar. The complex educational seminar is based on a review of the literature and on own extensive qualitative research. The seminar addresses the most challenging situations in the decision-making relating to antibiotic prescribing in general dentistry. It includes condensed transfer of relevant knowledge on bacterial resistance, pharmacology, and prophylaxis of infectious endocarditis; in-depth discussion on dentist-patient communication using three video-taped examples of poor, good, and elaborated dentist-patient communication on antibiotic treatment—the discussion particularly aims at elaborating strategies to satisfy dentists’ and patients’ needs for safety without prescribing non-indicated antibiotics; improved collaboration between dentists, general practitioners, and practice-based cardiologists by means of a standard fax form to agree upon the need for an antibiotic prophylaxis of endocarditis; antibiotic prescribing feedback that will be provided every six months, and will enhance dentists’ awareness of their own prescribing habits compared to those of their colleagues; and patient-centred information material to be used in the dentists’ practices. The information on the necessity to use or not use an antibiotic prophylaxis of endocarditis shall increase patients’ knowledge on antibiotic treatment.

### Control group

During the trial, the dentists of the control group receive neither the seminar nor the information material. They will provide care as usual. After the trial, the dentists of the control group will be invited to take part in the seminar.

### Outcomes

Primary outcome is the overall antibiotic prescribing rate of the intervention group and the control group measured at T1, thus measured in the interval between months one to six after intervention. A number of secondary outcomes will be analyzed for the subgroup of patients suffering from odontogenic infections (see below).

### Sample size

Data from Northern Germany shows that about 6% of all patients cared for in general dentistry receive antibiotics [11]. A relative reduction of 20% is perceived as both clinically relevant and attainable. For comparison, the previous CHANGE cRCT on antibiotic prescribing in German primary care reached a relative reduction of 40% [14]. The estimated intra-class correlation coefficient (ICC) of the prior CHANGE trial was employed for sample size calculation in this trial. In a RCT randomising at patient level and aiming at a reduction of antibiotic prescribing from 6% to 4.8% (a relative reduction of 20%) about 5,750 patients per group are necessary (power = 80%, level of significance (two-sided) α = 5%). Using an ICC of 0.2 and a cluster size of 1,000 patients the sample size needs to be adjusted with an average design factor of 4. Thus a total sample size of 46,000 patients in 46 dental practices is necessary for the trial. Assuming a dropout rate of 20% initially, 58 practices need to be recruited for baseline (see Figure 1).

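### The design factor of 4 does not follow from the stated ICC of 0.2 and 1,000 patients per practice: those inputs give about 201, and 46 practices then have about 6–7% power, not 80%

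*Protocol article*

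**What the plan says.** All figures are in the Protocol article, Methods, Sample size, unless noted.

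- Control rate: "about 6% of all patients cared for in general dentistry receive antibiotics".
- Effect: "aiming at a reduction of antibiotic prescribing from 6% to 4.8% (a relative reduction of 20"%).
- Size under individual randomisation: "about 5,750 patients per group are necessary", with "power = 80%, level of significance (two-sided) α = 5"%.
- Clustering: "ICC of 0.2 and a cluster size of 1,000 patients the sample size needs to be adjusted with an average design factor of 4". The ICC is said to be the estimate from an earlier cluster-randomised trial on antibiotic prescribing in German primary care.
- Result: "Thus a total sample size of 46,000 patients in 46 dental practices is necessary for the trial", raised to 58 practices for 20% dropout.

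The Trial design section defines a cluster as one practice with all its patients in the period, which agrees with 46,000 / 46 = 1,000. The Recruitment section gives the size of the pool: "All general dentists with a practice in and around 150 kilometers of Rostock (n = 665").

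**The concern.** One sentence gives two inputs and a result that does not follow from them. The design factor multiplies the whole sample size, so the patient total, the 46 practices and the 58 to be recruited all depend on it, as does the claim of 80% power for a 20% relative reduction.

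If the ICC of 0.2 is meant, the trial has almost no power for its stated target, yet readers are told that it is adequately powered. If the factor of 4 is meant, the calculation relies on an ICC that the article neither states nor justifies. A reader cannot tell which case applies, so the stated power gives no guidance on how to read a T1 result that shows no difference.

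**Working it through.** **Inputs from the Sample size section:** p1 = 0.06, p2 = 0.048, two-sided α = 0.05, power 80%, ICC = 0.2, m = 1,000 patients per practice, 46 practices. **Assumptions:** 1:1 allocation (implied by equal groups), equal practice sizes, ICC on the proportion scale, and no baseline adjustment, since the calculation takes no credit for any.

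**Step 1. Reproduce the plan's figures.** The pooled two-proportion formula gives 5,568 per group, and with continuity correction about 5,734. The stated 5,750 is sound. Then 2 × 5,750 × 4 = 46,000 patients, 46,000 / 1,000 = 46 practices, and 46 / 0.8 = 57.5, so 58. Every step reproduces once the factor of 4 is accepted.

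**Step 2. Design factor.** 1 + (m − 1) × ICC = 1 + 999 × 0.2 = 200.8.

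**Step 3. What a factor of 4 would need.**
- At m = 1,000: ICC = 3 / 999 = 0.0030.
- At ICC 0.2: m = 1 + 3 / 0.2 = 16 patients per practice.

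**Step 4. Power on the stated inputs.**
- Effective patients per arm: 23,000 / 200.8 = 114.5 (about 229 in total).
- Standard error: √[(0.06 × 0.94 + 0.048 × 0.952) / 114.5] = √(0.1021 / 114.5) = 0.0299.
- Effect / SE: 0.012 / 0.0299 = 0.40.
- Power: Φ(0.40 − 1.96) = 6.0% in the favourable tail, 6.9% counting both tails, and 6.8% from a t test on 44 df.

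**Step 5. Practices needed for 80% at ICC 0.2.** 2 × 5,750 × 200.8 / 1,000 = about 2,309 before dropout (about 2,236 without continuity correction). Enrolling all 665 eligible dentists as practices of 1,000 gives about 33% power.

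**Step 6. Is an ICC of 0.2 plausible here?** The implied between-practice SD is √(0.2 × 0.06 × 0.94) = 0.106, or 10.6 percentage points around a mean of 6%. That is hard to credit for a practice-level prescribing rate.

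**Step 7. Range over the ICC** (46 practices of 1,000, no baseline adjustment):

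| ICC | Design factor | Power |
|---|---|---|
| 0.003 | 4.0 | 81% |
| 0.005 | 6.0 | 64% |
| 0.01 | 11.0 | 40% |
| 0.02 | 21.0 | 24% |
| 0.05 | 51.0 | 12% |
| 0.2 | 200.8 | 6–7% |

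Reading 0.2 as a misprint for 0.02 therefore does not recover the plan (24% power, about 241 practices needed). Reading it as a logit-scale ICC does not either: the proportion-scale value is then about 0.054, the factor about 54, power about 12%, and about 626 practices are needed.

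**Step 8. Unequal practice sizes.** As an illustrative assumption, take a coefficient of variation of 0.5 at ICC 0.003. The factor becomes 1 + (1.25 × 1,000 − 1) × 0.003 = 4.75 and power falls to about 74%.

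**The case against.** The best counter-argument accepts the arithmetic but disputes what follows from it. The 6–7% holds only if the ICC is the correct entry and the factor of 4 the wrong one, yet an ICC of 0.2 is the less credible of the two; if the factor of 4 is right, power is about 81%. This stands as a limit on the conclusion. The article does not show which number is wrong, so the two results belong side by side.

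The second argument is that the design collects six months of baseline rates and stratifies on them, which the unadjusted figures ignore. Suppose the design factor scales by 1 − r², where r is the practice-level T0–T1 correlation (an assumption). Then ICC 0.01 with r = 0.8, or ICC 0.02 with r = 0.9, brings the factor to about 4 and power to 81–82%. This also stands in part: the middle rows of the table may understate the power of an adjusted analysis. It does not rescue the printed inputs. At ICC 0.2, r = 0.8 gives about 10% power and r = 0.9 about 15%; a factor of 4 needs r of about 0.99. The Sample size section claims no such credit, and the Statistical methods section makes baseline adjustment conditional on significant baseline differences.

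Third, once T1 data exist, their confidence interval, and not a planning ICC, shows what the trial can exclude. That is true, but it does not make the published power statement correct.

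Finally, a journal article condenses its protocol. That would excuse a missing figure, but these figures are printed and conflict with one another.

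**Conclusion.** The concern holds. An ICC of 0.2, 1,000 patients per practice and a design factor of 4 cannot all be true, and no standard reading of the section reconciles them. On the stated ICC and practice size the factor is 200.8 and power is about 6–7% rather than 80%. This rests on the ICC being literal and on the proportion scale, on equal practice sizes and on no baseline adjustment. If the factor of 4 is what was meant, power is about 81%, but only with an unstated ICC of about 0.003, and a modest departure to 0.005 already lowers unadjusted power to 64%. The rest of the calculation is sound. Because the only stated basis for 80% power on the primary outcome fails as written, this must be corrected.

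**What to change.** 1. Correct the Sample size paragraph. Either report the factor that follows from ICC 0.2 (200.8) with the power it leaves, or state and justify the ICC that a factor of 4 requires (about 0.003).
2. The Trial status section reports that baseline data are complete. From the pooled T0 data, without using allocation, estimate the ICC on the proportion scale, the mean prescribing rate and the spread of practice sizes.
3. Use these to restate the power, or the detectable difference, for the practices actually randomised under the T0-adjusted analysis, with the assumed T0–T1 correlation given.

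The practices are already randomised and T1 is under way, so no further recruitment is proposed, and allocation and outcome stay as they are. The cost is one short calculation on data in hand and a corrected paragraph. The restated power may be less favourable than 80%.
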